### Objectives {7}

The primary objective of our parallel randomized controlled trial is to evaluate the efficacy and acceptability of an intensive 3-week VRCET-based psychotherapy (VRCET +), i.e., VRCET + MFCT, in reducing self-reported cocaine craving in inpatients hospitalized for CUD, by comparing its immediate post-treatment effects to the ones of a traditional PCET.

The secondary objectives of our trial will be:To evaluate the effects after 2 weeks of treatment (V1; VRCET vs. CET), post-treatment (V2; VRCET + vs. PCET), and 1-month post-treatment (V3; VRCET + vs. PCET) on urinary, physiological, and self-reported measures of cocaine use-related measures (abstinence, risk of relapse, self-efficacy to cope with craving, emotional dysregulation, and identification to dysfunctional thoughts)To evaluate the effects of VRE to cocaine cues on cue-specific cocaine craving-related measures (cocaine craving, emotional states, self-efficacy to cope with craving) and cue-exposure specific measures (sense of presence, ecological validity, cybersickness) compared to a traditional non-VR pictures-based cue-exposure (PCE).To evaluate the cognitive, behavioral, or emotional factors (cocaine craving, self-efficacy to cope with craving, dysfunctional thoughts, cocaine use and emotional dysregulation) mediating the efficacy of VRCET + in decreasing self-reported cocaine craving.To evaluate the acceptability of (i) our intensive VRCET as a stand-alone (V1) or add-on (V2; VRCET +) therapeutic intervention via client satisfaction towards psychotherapeutic services measures and (ii) VRE, as a cue-exposure paradigm via cybersickness self-reported measures.

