### Criteria for discontinuing or modifying allocated interventions {11b}

Participants will be able to discontinue their participation any time during the protocol. The principal investigator will oversee documenting reasons of early cessations thoroughly. The principal investigator will be allowed to permanently end any participation in the study, for any reason putting at significant risk participant safety or compliance to the protocol. Criteria for discontinuation include:Long-term hospitalization (> 1 month) for other than CUDAbsence to 3 consecutive sessions

In case of discontinuation, the data collected will be analyzed and the participants will not be substituted.

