The dispersion of blood pulse, skin temperature, and conductance signals will be used through PLUX Biosignals physiological captors (medical device certification: ISO 13485) to assess the cue-specific reactivity in VRCE compared to PCE.The CEQ-S mean total scores will be used to subjectively assess cocaine craving intensity in participants exposed to VRCE compared to PCE; items range from 11 (“not at all”) to 110 (“extremely”; [54]).The Brief Mood Introspection Scale (BMIS) mean total scores will be used to subjectively assess negative and positive emotional states in participants exposed to VRCE compared to PCE. Items range from 0 (“definitely do not feel”) to 21 (“definitely feel”; negative emotions) or 27 (positive emotions; [60]).The Drug Taking Confidence Questionnaire – 8 (DTCQ-8) mean total scores will be used to subjectively assess the self-efficacy to cope with cocaine craving in participants exposed to VRCE compared with PCE; items range from 0 (“not at all confident”) to 800 (“very confident”; [61]).The Spatial Presence for Immersive Environments (SPIE) – Spatial Presence subscale mean total scores will be used to subjectively assess the sense of presence experienced by participants exposed to VRCE compared with PCE; items range from 4 (“strongly disagree”) to 20 (“strongly agree”; [62].The Spatial Presence for Immersive Environments (SPIE) – Realism subscale mean total scores will be used to subjectively assess the increased sense of reality experienced by participants exposed to VRCE compared with PCE, ranging from 4 (“strongly disagree”) to 15 (“strongly agree”; [62]).The Independent Television Commission Sense of Presence Inventory (ITC-SOPI) – Ecological Validity subscale mean total scores will be used to subjectively assess the increased sense of ecological validity experienced by participants exposed to VRCE compared to PCE; items range from 5 (“strongly disagree”) to 25 (“strongly agree”; [25]).Assessing the cognitive, behavioral, or emotional factors (cocaine craving, dysfunctional thoughts, cocaine use, and emotional dysregulation) mediating the efficacy of VRCET+ in decreasing self-reported cocaine craving. The CEQ – F, QCBDU, TLFB, and DERS mean total scores will be used to subjectively assess, as aforementioned, cocaine craving frequency (last 14 days), dysfunctional thoughts regarding CUD, cocaine abstinence (last 21 days), and difficulties in emotion regulation.Assessing the acceptability of (i) our intensive VRCET as a stand-alone (after 2 weeks of treatment; V1) or add-on (post-treatment; V2; VRCET +) intervention and (ii) VRE as a cue-exposure paradigm, for each new VRE performed in therapy.The Spatial Presence for Immersive Environments (SPIE) – Cybersickness subscale mean total scores will be used to subjectively assess acceptable cybersickness symptoms (i.e., < 7) experienced by participants exposed to VRCE; items range from 0 (“strongly disagree”) to 10 (“strongly agree”; [62]).The Client Satisfaction Questionnaire – 8 (CSQ-8) mean total scores will be used to subjectively assess satisfaction levels towards psychotherapeutic services (≥ 21; “good”); items range from 8 to 32 [63].

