### Methods in analysis to handle protocol non-adherence and any statistical methods to handle missing data {20c}

Given the small target sample size (*n* ≈ 50) and in case of arbitrary pattern of missing data, if applicable, multiple imputations for incomplete multivariate data will be performed on all missing data, using the *Amelia R* package [69, 70]. Our comprehensive imputation *R* code will be made available.

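### Acceptability of the therapy rests on CSQ-8 at two treatment sessions alone: patients who stop before a session have no scheduled score there, and stopping is not itself an acceptability outcome

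*Protocol article*

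**What the plan says.** The primary objective (protocol article, Objectives {7}) is to "evaluate the efficacy and acceptability of an intensive 3-week VRCET-based psychotherapy". Secondary objective 4 then divides acceptability in two. The therapy itself, VRCET at the 2-week visit and VRCET+ at the end of treatment, is judged as a "therapeutic intervention via client satisfaction towards psychotherapeutic services measures". The VR exposure is judged separately: "VRE, as a cue-exposure paradigm via cybersickness self-reported measures".

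Outcomes {12} names CSQ-8 as the satisfaction measure: "The Client Satisfaction Questionnaire – 8 (CSQ-8) mean total scores will be used to subjectively assess satisfaction levels towards psychotherapeutic services". The label and range follow: "satisfaction levels towards psychotherapeutic services (≥ 21; “good”); items range from 8 to 32". Table 4 schedules it at weeks 2 and 3 only, with nothing at baseline, at follow-up or at early exit. The section on in-treatment and post-treatment measuring times places T1 at the 11th treatment session and T2 at the 15th and last.

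On stopping, section {11b} says "The principal investigator will oversee documenting reasons of early cessations thoroughly". It lists three consecutive missed sessions and a long hospitalization for a reason other than CUD as discontinuation criteria, and it provides for analysing the data collected. On missing values, section {20c} says that, given an arbitrary pattern and if applicable, "multiple imputations for incomplete multivariate data will be performed on all missing data".

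**The concern.** A patient who finds the therapy unacceptable may stop coming, and CSQ-8 is collected only at sessions that such a patient no longer attends. The scale then describes mainly those who tolerated the therapy well enough to stay. The protocol documents why patients stop, but it does not turn stopping, its reasons or attendance into an acceptability outcome.

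At stake is the acceptability conclusion, which is part of the primary objective's wording and is made operational in secondary objective 4. The primary outcome, craving on the CEQ, is not affected by this point.

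**Working it through.** **1. Who has a satisfaction score.** Objectives {7}, Outcomes {12}, Table 4 and the visit timing give:

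| Patient | CSQ-8 at T1 | CSQ-8 at T2 |
|---|---|---|
| Completes treatment | scheduled | scheduled |
| Stops between T1 and T2 | scheduled | none |
| Stops before T1 | none | none |

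**2. Whether the second measure fills the gap.** SPIE-Cybersickness is taken at each new VR exposure, so leavers contribute until they stop. However, the objectives assign it to VR exposure as a paradigm. The Non-inclusion criteria also exclude patients scoring 7 or more in the tutorial, the same cut-off that Outcomes {12} uses for acceptable symptoms. It does not capture dislike of the therapy for other reasons.

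**3. Whether imputation fills it.** Section {20c} is conditional on an arbitrary pattern of missing data, whereas dropout usually gives a monotone one. Standard multiple imputation assumes data missing at random, which fails if dissatisfaction itself causes the exit. Two cases differ:
- Stopping between T1 and T2: the patient's own T1 CSQ-8 and other T1 scores can inform the imputed T2 value.
- Stopping before T1: CSQ-8 has no baseline value, so the patient has no satisfaction score. The link between CSQ-8 and the other variables must then be learned entirely from patients who stayed.

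**4. Possible size.** The protocol states no dropout rate and no expected CSQ-8 mean, so it has no figure to reproduce, and the inputs below are assumptions. Let q be the proportion stopping, mc the completer mean and ml the mean that leavers would have given.

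All-randomized mean = (1 − q) × mc + q × ml

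Overstatement by the completer mean = q × (mc − ml)

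With mc = 25:

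| q | ml = 20 | ml = 16 | ml = 12 |
|---|---|---|---|
| 10% | 0.5 | 0.9 | 1.3 |
| 20% | 1.0 | 1.8 | 2.6 |
| 30% | 1.5 | 2.7 | 3.9 |
| 40% | 2.0 | 3.6 | 5.2 |

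**5. Whether the label for good satisfaction (21 or more) would change.** Each arm has 54/2 = 27 patients (Sample size {14}; 1:1 allocation in {16a}). With k leavers, each assumed to score 14, the all-randomized mean is (14k + (27 − k) × mc)/27:

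| k | mc = 22.5 | mc = 25 |
|---|---|---|
| 3 | 582/27 = 21.6 | 642/27 = 23.8 |
| 5 | 565/27 = 20.9 | 620/27 = 23.0 |
| 8 | 539.5/27 = 20.0 | 587/27 = 21.7 |

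With mc = 22.5, five leavers bring the mean just under 21. With mc = 25, even eight do not. With mc = 25 and leavers at 12, the mean falls below 21 once q exceeds (25 − 21)/(25 − 12) = 0.31.

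**The case against.** The strongest reply is that the protocol defines acceptability explicitly and consistently, and that satisfaction plus cybersickness is a legitimate choice. Nothing is misstated. Stopping is also a mixed signal: hospitalization for another reason, or withdrawal by the investigator on safety grounds, need not reflect the patient's view of the therapy. Because reasons are documented, stopping can be reported without new data. Participants are inpatients and may still be reachable after they stop, and section {11b} does not forbid an exit assessment.

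Much of this stands, and it limits the point. Stopping should not be read as rejection unless the reason is examined. What remains is that no acceptability outcome uses stopping, and that satisfaction is scheduled only at sessions leavers do not attend. The choice and timing of the outcome are stated in the article itself, so this is not a detail left to a fuller document.

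Three stronger readings are tempting, and the documents do not support them:
- That acceptability as a whole rests on satisfaction ratings. Cybersickness is a second measure, to which leavers contribute until they stop.
- That all missing satisfaction scores would be filled in from patients who stayed. This is close to true only for those leaving before T1, since later leavers have their own T1 data.
- That the trial will wrongly declare the therapy acceptable, or that a planned comparison of acceptability with PCET is distorted. The value 21 labels a satisfaction level and is not stated as a pass mark for an arm mean. Whether it is crossed depends on the assumed completer mean. Secondary objective 4 names no PCET contrast.

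**Conclusion.** The point holds as a limitation of the outcome definition. Acceptability of the therapy is measured only by CSQ-8 at the 11th and 15th sessions, so the observed mean overstates satisfaction if leavers are less satisfied than those who stay. The direction follows from that one assumption. The size cannot be determined from the protocol: under the illustrative values it runs from 0.5 points (10% stopping, leavers at 20) to 5.2 points (40% stopping, leavers at 12) on a scale from 8 to 32. The planned imputation may help for patients who leave after T1, but it cannot be relied on for those who leave before. This is an inexpensive improvement to a stated objective, not an error that undermines the trial.

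**What to change.** - Add as acceptability outcomes, for all randomized patients and by arm, the proportion who stop the allocated therapy before T1 and before T2, and the number of sessions attended.
- Use the reasons already documented under {11b} to separate stopping related to the therapy from unrelated causes, such as hospitalization for another reason.
- Offer CSQ-8 when a patient stops early.
- Report CSQ-8 beside the stopping rate, and do not base the acceptability conclusion on CSQ-8 values imputed for patients who left before T1.

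The cost is a change of outcome wording and one 8-item form at exit. Some leavers will decline the form, but the stopping rate would still cover every randomized patient.

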
### Participant timeline {13}

#### Inclusion visit (V0)

Every patient treated for CUD at one of the two investigations centers and deemed potentially eligible for study inclusion will be informed by their assigned psychiatrist about the study’s objectives, protocol implications, and expected therapeutic benefits. Each patient will be invited to the inclusion visit (V0) during which the necessary information for giving informed consent to participate will be provided. The dates of the written consent as well as its withdrawn (if applicable) will be documented in their medical record. During this inclusion visit, the research psychiatrist or psychologist will oversee the examination of study eligibility for patients (e.g., Significant SCID-5 CV score for CUD; URICA self-questionnaire score ≥ 11; Non-significant M.I.N.I.5. (DSM-IV) score for current high suicidal risk, post-traumatic stress, psychotic, mania or hypomania episode; Post-VRE SPIE—Cybersickness score ≥ 7).

#### Randomization

Eligible patients will be randomized by the research psychiatrist or psychologist in charge of the inclusion visit, using the Research Electronic Data Capture (REDCap) secure web application, in the VRCET + (experimental) or PCET (active control) therapeutic arm.

After randomization, participants will be invited to complete baseline self-reported measures as well as to perform a craving induction task related to primary and secondary research objectives. This craving induction task will consist of three 7-min 30 exposures and will systematically start with one VRE to neutral cues, followed by one VRE and one PCE to a cocaine-related situation. The order of these two exposures to cocaine cues (i.e., VRE thus PCE or PCE thus VRE) will be randomly counterbalanced for controlling for potential cue-induced carry-over effect between one exposure to the other. The exposures’ order sequence generation for each participant will be generated by the research methodologist, using the Research Randomizer secure web application, and provided to the investigator within sealed opaque envelope for the inclusion visit.

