### Outcomes {12}

Our primary outcome will consist in the decrease of the self-reported cocaine craving as assessed with the French Craving Experience Questionnaire (CEQ; [53, 54]. The CEQ is an 11-item retrospective measure of cocaine craving containing two subscales: craving strength (CEQ-S) and frequency (CEQ-F). Each item is completed by the participants on a 10-point scale, from “not at all” (1) to “extremely” (10). The CEQ has shown good psychometric properties [54]. Means of CEQ-S and CEQ-F total scores will be analyzed. Finally, the CEQ will be administered before treatment (V0), after 2 weeks of treatment (V1; VRCET vs. PCET), post-treatment (V2; VRCET + vs. PCET), and 1-month post-treatment (V3; VRCET + vs. CET). The CEQ-S will be administrated immediately after a 7-min VRE to a cocaine-related situation, with a similar scenario to the CET situation 5 (Table 1) but across different virtual environments, avatars, and item appearances (Fig. 9). The CEQ-F will be administrated retrospectively, targeting the last 14-day period. (Table 4)

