### Concealment mechanism {16b}

The research psychiatrist or psychologist will be informed of the participant allocation only at the start of the intervention phase, following a sealed opaque envelope-based procedure.

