### Implementation {16c}

The allocation sequence will be generated by the research data manager from the UHM methodology unit before starting the research and following a confidential handbook document. Each research psychiatrist and psychologist will oversee the assignment of participants to interventions in their respective investigation center.

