## Assignment of interventions: blinding

### Who will be blinded {17a}

Patients and researchers will not be blinded after assignment to interventions given significant delivery modalities between VR-based and picture-based exposure therapies. Only the data manager in charge of the allocation sequence will be blinded to the assignment.

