### Confidentiality {27}

Any study professional member (e.g., research psychiatrist, psychologist, or data manager) having access to participants’ individual data will be bound to professional secrecy, which is in accordance with the French public health code. The use of participants’ individual data collected will be systematically anonymized following a codification participant identification procedure. To do so, each code generated for each participant will include the center in which the investigation is conducted (UHM or SEH), the intervention assignment (experimental or active control arm), and the inclusion number (e.g., 001), following a chronologic sequence. Each principal investigator will oversee the confidentiality of the data using a sealed paper-based record in which participant authentication data (first name, family name, and date of birth) will be related to their identification code.

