## Statistical methods

### Statistical methods for primary and secondary outcomes {20a}

Statistical analyses for principal and secondary outcome will be computed from self-report scales raw total scores or physiological signals (i.e., blood pressure, skin temperature and conductance) using, respectively, R Statistical [66] and OpenSignals (© PLUX S.A.) software. Our comprehensive data working R code, including R packages and inferential statistical hypothesis testing assumptions (Gaussian distribution, homoscedasticity, etc.), will be made available. For each primary or secondary variable of interest, descriptive statistics (n, min, max, median, q1, q3, iqr, mean, sd, se, and mean ci) will be computed using the *rstatix R* package. Primary inferential statistical analyses will consist of two-tailored independent *t*-tests on score changes between T0 (baseline) and T2 (post-treatment) in the experimental (i.e., VRCET +), compared with the active control therapeutic arm (PCET). In case of mostly non-normal variable distributions but symmetrical score differences around the median, Friedman and Bonferroni-corrected Wilcoxon signed-rank tests will be performed to test and contrast score differences between the conditions using *stats* and *rstatix R* packages [67]. In case of non-symmetrical paired score differences, Bonferroni-corrected Sign tests will be performed. Causal mediation analyses will be adjusted for confounding factors. Cohen’s d, Kendall’s W, and Cliff’s delta effect sizes for score changes across treatment arms (“negligible,” “small,” “medium,” and “large” effect for Cliff’s d inferior to 0.15, 0.33, 0.47, and superior to 0.47; [68]) with 95% CIs will be computed using *irr* and *effsize R* packages.

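### Baseline craving, one of the two measurements in the primary change score, is taken after randomisation in an open-label trial, and the plan does not settle who knows the arm by then

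*Protocol article*

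**What the plan says.** The Randomization section (under Participant timeline {13}) fixes both the actor and the order. On the actor: "Eligible patients will be randomized by the research psychiatrist or psychologist in charge of the inclusion visit", using REDCap. On the order: "After randomization, participants will be invited to complete baseline self-reported measures as well as to perform a craving induction task". Table 4 puts allocation and the baseline assessments together at T0, Week 0.

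Outcomes {12} defines the endpoint: "Our primary outcome will consist in the decrease of the self-reported cocaine craving as assessed with the French Craving Experience Questionnaire". Both subscales are taken at V0, with CEQ-S following a virtual-reality exposure. Statistical methods {20a} sets the primary analysis as "independent *t*-tests on score changes between T0 (baseline) and T2 (post-treatment"), experimental arm against control.

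Four further sections bear on who knows the allocation:

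- Concealment mechanism {16b}: clinicians on the trial team "will be informed of the participant allocation only at the start of the intervention phase, following a sealed opaque envelope-based procedure"; this covers staff only.
- Implementation {16c}: "Each research psychiatrist and psychologist will oversee the assignment of participants to interventions in their respective investigation center".
- Who will be blinded {17a}: "Patients and researchers will not be blinded after assignment to interventions".
- Confidentiality {27}: the participant code is built from the centre, "the intervention assignment (experimental or active control arm), and the inclusion number".

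**The concern.** A baseline is safe from the allocation when it is recorded before the allocation exists, or at least before anyone involved in recording it knows the allocation. Here it is recorded after the allocation exists. Whether it is recorded before the allocation is known depends on which section describes practice.

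The outcome is a self-report, so what the patient knows matters as much as what staff know. A patient who has learned that the next three weeks will bring pictures, or virtual reality, may rate craving differently. T0 is subtracted from T2, so a difference between arms created in this way at T0 would count as part of the treatment effect. It could not be recovered afterwards, because no uncontaminated baseline would exist.

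**Working it through.** **Step 1: the sections side by side.**

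| Question | Randomization, {16c}, {17a} | {16b} |
|---|---|---|
| Who carries out the allocation? | Inclusion-visit clinician in REDCap; centre clinicians oversee assignment | Sealed opaque envelope |
| When do research staff know the arm? | Implied at V0 by carrying out the randomisation; open after assignment | Only when the intervention starts |
| When does the patient know the arm? | Open after assignment; no time given | Not addressed |

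Therapy starts within 1 week after the inclusion visit. If {16b} governs, staff record T0 without knowing the arm. If the Randomization section and {16c} describe practice, they may know it. The envelope mentioned in the Randomization section carries the order of the two cue exposures, not the arm, so it does not resolve the conflict. On neither reading is the patient's knowledge at T0 settled.

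**Step 2: how a T0 shift reaches the result.** Let s0 and s2 be the between-arm differences in reporting, caused by knowing the arm, at T0 and T2. The bias in the change score is s2 − s0. If the shift has gone by T2 (s2 = 0), the whole T0 shift enters. If it persists unchanged (s2 = s0), it cancels.

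**Step 3: an illustration of size.** The plan gives no figure for this, so there is none to reproduce. The inputs are:

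- from Sample size {14} and Sequence generation {16a}: 54 randomised 1:1, so 54/2 = 27 per arm, and a two-sided threshold of 0.05;
- assumed: all 54 analysed, no true effect, equal SDs at T0 and T2, pre-post correlation ρ, and a T0 shift of b raw-score SDs that has gone by T2.

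The SD of the change is √(2(1 − ρ)) raw SDs, so the standardised shift is d = b/√(2(1 − ρ)). The t-test has 52 degrees of freedom and noncentrality d·√(27/2) = 3.674·d. At ρ = 0.5 the divisor is 1, so b = 0.1, 0.2 and 0.3 give noncentralities of 0.367, 0.735 and 1.102. The two-sided rejection probabilities, for each t-test taken on its own, are:

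| Assumed T0 shift (SD) | ρ = 0.3 | ρ = 0.5 | ρ = 0.7 |
|---|---|---|---|
| 0.1 | 0.061 | 0.065 | 0.075 |
| 0.2 | 0.094 | 0.111 | 0.154 |
| 0.3 | 0.150 | 0.191 | 0.287 |

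**Step 4: would adjusting for baseline help?** With T0 as a covariate, the same shift leaves a bias of ρb against a residual SD of √(1 − ρ²). At ρ = 0.5 and b = 0.3 this is 0.15/0.866 = 0.173, and the rejection probability is 0.096 instead of 0.191. At b = 0.2 it is 0.070 instead of 0.111. Adjustment reduces the problem but does not remove it.

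**The case against.** The strongest reply is {16b}. If staff do not learn the arm until therapy starts, V0 is complete before they know it, and randomising first does no harm through them. Nor does {17a} say that the arm is disclosed at V0: it explains the lack of blinding by the difference in delivery, which shows once sessions begin. This stands as far as it goes. It makes contamination a possibility and not a fact. It does not cover patients, and it does not explain how a clinician who randomises in REDCap stays unaware of the result.

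A reader might infer several stronger things that the documents do not support:

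- *That the randomising clinician also collects the baseline.* The shared visit suggests it, but it is not stated. Outcomes are mostly paper self-reports, and {18a} refers to trained study assessors.
- *That the participant code defeats {16b}.* Confidentiality {27} gives the format of the code but not when it is issued or whether the baseline forms carry it.
- *That staff can guess the next allocation.* Permuted blocks within centre are stated, but no block size is. This would also be a selection problem, separate from the baseline.
- *That the bias equals the T0 shift and favours the experimental arm.* It equals the T0 shift only if the shift has gone by T2. The direction is also open: if PCET patients report more craving at T0 out of disappointment, PCET shows the larger fall and the bias runs against VRCET+.
- *That patients who withdraw on learning their arm have no baseline.* This presumes disclosure before the V0 measures, which no section states.

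**Conclusion.** The point holds as a fault of sequence and an internal contradiction. The plan sets T0 craving after randomisation in an open-label trial with a self-reported change score. Its one safeguard conflicts with the sections on who randomises and who oversees assignment, and that safeguard does not mention patients. The T0 self-report is therefore unprotected from knowledge of the allocation. A reader might go further and call the baseline biased, but the documents do not establish that.

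The size is illustrative. At a correlation of 0.5, shifts of 0.1 to 0.3 SD take the type I error from 0.05 to between about 0.065 and 0.19. The shifts, the correlation, complete follow-up and the disappearance of the shift by T2 are all assumptions. The order of events and the conflict between sections rest on the text alone.

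**What to change.** At V0, complete eligibility, consent, all baseline questionnaires and the craving-induction task, and make the REDCap randomisation the last step. Therapy starts up to a week later, so the timetable allows this. Reconcile the Randomization section, {16b}, {16c} and {17a} in one statement of who learns the arm and when, covering patients as well as staff, and of how REDCap and the envelopes fit together. Keep the arm out of the participant code, at least until baseline is recorded.

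The sample size stays at 54, and no assessment or staff are added. The cost is a re-sequenced visit, a change to the code format and a protocol amendment. Recruitment began in May 2023, so patients already enrolled under the present order form a second baseline regime. They should be flagged, and a sensitivity analysis should show whether the result depends on them.
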